#### xiv. Bias minimization procedures

To reduce bias, evaluations of participants will be done in a blinded manner (i.e. without knowledge of whether they belong to a SDTT group or a SDTT+ group, or whether the participant will take part in a second baseline measurement). Any data collection at To will be done before the assignment of a patient. The clinical assessment at T1 and T2 will be run by personal, which will not know the group the participant was assigned to. Quantitative outcome parameters (e.g. EEG parameters or gait outcomes) are not prone to be bias.

#### xv. Specific administrative procedures

##### **Withdrawal from the study**

All participants remain free to withdraw at any time from the trial without giving reasons and without prejudicing their further treatment and must be provided with a contact point where he/she may obtain further information about the trial. Participants will be informed, that upon request all data collected up to the point of withdrawal will be permanently deleted.

##### **Reimbursement policy**

Participants can receive reimbursement of reasonable expenses, according to local guidelines. Travel expenses may include own vehicle, public transport or taxi.

#### xvi. Data management procedures

To make data management GDPR compliant, we will use the VU research drive, hosted by the VU in Amsterdam, Netherlands to provide a central access point to protocols, standards and workflows, and to streamline the creation and curation of a central data asset based on the FAIR (Findable, Accessible Interoperable and Reusable) principles. To ensure high standards of data processing, the widely accepted Brain Imaging Data Structure (BIDS) standard to store the motion, EMG and EEG data will be followed. A Github repository will be established to facilitate code sharing and a communication channel will be established to facilitate day to day interactions between partners. The channel will specifically support early-career researchers, to enhance knowledge transfer, skills sharing and mentoring across the network. Code developed in WP2 and WP3 for data analysis will be fully shared in the consortium and will be made publicly available upon publishing results, via the MJFF and OpenNeuro.

Participant data will be collected in a coded, de-identified manner. Data will be stored on a RedCap server hosted in the EU in a standardized form across the StepuP consortium. This data will be organized following BIDS standards. Only pseudonymized data will be shared between partners using European servers.

All recruitment sites will keep original records of all signed consent forms, trial key codes, and any other paper forms or samples that are collected at source, under secure conditions at the site or origin until the trial has been completed and the database has been locked. After this

point, these documents can be purged or archived for a further period, depending on local requirements.

Direct access will be granted to authorized representatives from the PI, host institution and the regulatory authorities.

Clinical sites will be responsible to archiving all trial documents for a period of time that is in keeping with institutional or national guidelines that pertain to that site. Destruction of documentation should be notified to the PI.

#### xvii. End of trial

The end of trial will be defined date of the last visit/data item of the last participant undergoing the trial.

#### xviii. Dissemination policy

Dissemination of project results is crucially important to reach a long-lasting impact. StepuP has multiple measures in place to maximise dissemination of the results emphasising an Open Access policy and is committed to this goal by employing several strategies. Emphasizing an Open Access policy, the project actively participates in conferences to engage with relevant stakeholders, furthering the reach and understanding of its findings. In a notable move towards inclusivity, StepuP has also planned to invite patients to present the final results, aligning the research more closely with those directly affected. Moreover, the project recognizes the importance of media exposure and plans to utilise local channels (e.g. newspapers) for sharing information with the broader community.

## 6. Statistics and analysis plan

### i. Sample size calculation

The sample size was calculated using the SampSize applicationon for the clinical primary objective (i.e., comfortable gait speed overground, measured in m/sec from a 20 meters walking test), with a significance level (alpha) of 0.05 and power (1-beta) of 0.80, with an allocation ratio of 1:1 in parallel groups. From the available literature, it is known that standard treadmill (SDTT) may improve comfortable overground gait speed up to 0.1 m/sec (from a baseline of 1.26 m/sec) in comparison to standard overground walking and that SDTT with perturbations (SDTT+) may further increase comfortable overground gait speed up to +0.08 m/sec in comparison to SDTT. Thus, we will assume that SDDT+ is superior to SDTT at improving comfortable overground gait speed based on an expected average difference in gait speed between the two groups of +0.08 m/sec with a SD of 0.08 Under this assumption, 17 subjects per group are expected to be enrolled, rising to 20.4 considering a maximum drop-out rate of 20%. This would lead to 41 subjects per trial, rounded to 42 to allow for groups of equal size.

Overall, 126 patients at all clinical sites will in enrolled over a period of 24 months. The recruitment totals for each site is outlined in Table 2. Given the time frame of the trial, recruitment will be monitored on a monthly basis. Should any site encounter recruitment difficulties, other sites have the capacity to recruit additional participants for each cohort as well as to recruit additional cohorts if necessary.

### ii. Analysis plans and datasets

The statistical analysis of the outcomes will comprise the definition of analysis sets and statistical analysis (including prioritization of outcomes).

---

 <https://app.sampsize.org.uk>

The main aim is to determine the mechanisms underlying effects on gait performance in clinical tests and in daily-life of SDTT. This entails an analysis of pooled data (excluding the healthy control participants). Nested within this design, several randomized comparisons will be made to assess the added value of the SDTT+ components over SDTT. Initially a placebo comparison was planned but given the proven effect of SDTT this was deemed unethical. To interpret the any effects changes in the absence of a placebo control group it is first of all important to determine the minimal meaningful change for the outcome parameters. In addition, a comparison between participants with and without PD will be done to support interpretation of effects in the PD group. These analysis to this end are described as analysis 1a and 1b. Subsequently the nested randomized comparisons are described as levels 2a to 2c. Finally, the analysis to test hypothesis on the causality of changes in gait performance will be described as analyses 3a and 3b.

### iii. Descriptive analysis

Main characteristics of patients, including detailed description of walking capacity, will be done by number and percentage for categorical variables, mean and standard deviation for continuous variables with normal distribution, and median and percentiles 25th-75th for continuous variables with non-normal distribution.

### iv. Analysis of reliability (1a)

#### **Population:**

From the populations measured in Sydney 21 participants chosen at random will participate in an additional measurement set 14 days prior to start of the intervention (T-1). This sample is kept small for pragmatic reasons. First, it is not feasible to apply this additional measurement in all participants at all centers. Second, in case a systematic effect of repeated testing is found, this may need to be statistically corrected for or the sub-sample of individual participants with this additional baseline may need to be omitted in the pooled analyses (3a and 3b).

#### **Dependent variables:**

##### *primary clinical outcomes:*

- preferred gait speed (20 m walk test)
- stride length (at preferred speed)
- stride length (at 1.4 km/h)

##### *secondary clinical outcomes:*

- stride length variability (at preferred speed and at 1.4 km/h)
- stride time (at preferred speed and at 1.4 km/h)
- stride time variability (at preferred speed and at 1.4 km/h)
- step width (at preferred speed and at 1.4 km/h)
- step width variability (at preferred speed and at 1.4 km/h)
- falls (diary)
- timed-up-and-go (TUG) test
- 2-minute walk test
- MiniBESTest
- MOCA
- MDS-UPDRS, part III
- mGES

##### *feedback control variables (all at 1.4 km/h):*

- $R^2$  (feedback model relating foot placement to centre of mass movement)
- RMS error (feedback model relating foot placement to centre of mass movement)
- Position gain (feedback model relating foot placement to centre of mass movement)

- Velocity gain (feedback model relating foot placement to centre of mass movement)

*neural correlates (T1 all at 1.4 km/h):*

- EEG beta power in(pre-)motor areas during walking at preferred speed
- EEG-EMG coherence during walking at preferred speed

### **Analysis technique:**

Bland-Altman analyses will be performed to test for a systematic effect of repeated measurements (paired t-tests) and to establish the limits of agreement for the outcome variables. The limits of agreement thus established will provide the basis for evaluating any effect sizes found in analyses 2a-2c.

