**Dependent variables:**

*primary clinical outcomes:*

- preferred gait speed (20 m walk test)
- stride length (at preferred speed)
- stride length (at 1.4 km/h)

*secondary clinical outcomes (T1):*

- stride length variability (at preferred speed and at 1.4 km/h)
- stride time (at preferred speed and at 1.4 km/h)
- stride time variability (at preferred speed and at 1.4 km/h)
- step width (at preferred speed and at 1.4 km/h)
- step width variability (at preferred speed and at 1.4 km/h)
- falls (diary)
- timed-up-and-go (TUG) test
- 2-minute walk test
- MiniBESTest
- MOCA
- MDS-UPDRS, part III
- mGES

*secondary clinical outcomes (T2):*

- steps per day
- uninterrupted walk durations
- stride time variability
- symmetry

*feedback control variables (T1 all at 1.4 km/h):*

- $R^2$  (feedback model relating foot placement to centre of mass movement)
- RMS error (feedback model relating foot placement to centre of mass movement)
- Position gain (feedback model relating foot placement to centre of mass movement)
- Velocity gain (feedback model relating foot placement to centre of mass movement)

*neural correlates (T1 all at 1.4 km/h):*

- EEG beta power in(pre-)motor areas during walking at preferred speed
- EEG-EMG coherence during walking at preferred speed

Linear mixed effect models with the interaction of treatment and time in the model and a random intercept for participant nested within center (Twisk et al., 2018), controlling for relevant potential confounders (e.g., age, H&Y stage). For the EEG data, we will use cluster-based permutation tests time locked to the gait cycle.TT)

vii. Independent RCTs SDTT vs SDTT+ (3a)

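### Limits of agreement, which describe single patients, are made the yardstick for group effects, so a real between-arm benefit could be read as measurement noise

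*Protocol*

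**What the plan says.** Section 6.ii explains that no placebo arm was possible and that, for interpreting changes without one, "it is first of all important to determine the minimal meaningful change for the outcome parameters". Analysis 1a (section 6.iv) is one of the two analyses meant to serve that purpose. Its sample is described as follows: "From the populations measured in Sydney 21 participants chosen at random will participate in an additional measurement set 14 days prior to start of the" training. The technique is Bland-Altman, with a paired t-test for a systematic effect of repetition and limits of agreement for every listed outcome. The section ends: "The limits of agreement thus established will provide the basis for evaluating any effect sizes found in analyses 2a-2c".

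Section 6.ii calls 2a to 2c the nested randomised comparisons of SDTT+ with SDTT. Only 2a (section 6.vi) appears under such a label; the site-level comparison is headed 3a (section 6.vii). Analysis 2a uses "Linear mixed effect models with the interaction of treatment and time in the model and a random intercept for participant nested within center", so its target is a difference between arms in mean change.

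Section 6.i sizes each trial for an "expected average difference in gait speed between the two groups of +0.08 m/sec with a SD of 0.08". It does not say whether that SD refers to speed at one visit, to change, or to repeat measurement. The protocol gives no test-retest SD or correlation for gait speed and names no other yardstick for the size of a group effect.

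**The concern.** Limits of agreement answer the question: how far apart may two readings on one patient lie when nothing has changed? The answer depends on the SD of individual differences, and more patients only estimate it better. A between-arm difference in means asks a different question. Its uncertainty falls with the number of patients, and measurement noise is already in its standard error.

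Two further points weaken the link made in section 6.iv. First, the limits quantify noise. A change can exceed them and be unimportant to patients, or fall within them and matter as a group average, so they cannot supply the minimal meaningful change sought in section 6.ii. Second, the stated reason for the yardstick is the missing placebo arm. That reason fits uncontrolled pre-post change. In a randomised contrast, a retest effect common to both arms cancels.

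At stake is how the comparison of SDTT+ with SDTT is described. A statistically clear benefit of the planned size could be reported as lying within measurement error.

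**Working it through.** **1. The plan's own figure.** Inputs from section 6.i: difference 0.08 m/s, SD 0.08 m/s, alpha 0.05 (taken as two-sided, which reproduces the result), power 0.80, ratio 1:1. The two-sample t-test solution is 16.7, so 17 per group, as stated. Power is 80.7% at 17 per arm and 88.5% at 21 per arm.

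**2. Width of the limits.** Half-width = 1.96 × SD of the test-retest differences, taking the mean retest difference as zero. The SD is not in the protocol, so the values below are assumptions.

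| Assumed difference SD (m/s) | Limits (m/s) | Planned 0.08 m/s |
|---|---|---|
| 0.04 | ±0.078 | just outside |
| 0.05 | ±0.098 | inside |
| 0.06 | ±0.118 | inside |
| 0.08 | ±0.157 | inside |

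Break-even: 0.08 / 1.96 = 0.041 m/s.

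**3. If 0.08 is the SD of speed at one visit.** The difference SD is then 0.08 × √(2(1 − r)), with r the test-retest correlation. At r = 0.5 the limits are ±0.157, at r = 0.8 ±0.099 and at r = 0.9 ±0.070 m/s. Break-even is r = 1 − (0.0408/0.08)²/2 = 0.87.

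**4. Uncertainty of the group effect.** Standard error = SD × √(2/n), with SD 0.08, ignoring centre and covariates.

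| n per arm | Standard error (m/s) | 95% CI half-width (m/s) |
|---|---|---|
| 17 (evaluable, one trial) | 0.027 | 0.056 |
| 21 (enrolled, one trial) | 0.025 | 0.050 |
| 63 (all centres in Table 2, no dropout) | 0.014 | 0.028 |

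The pooled row is the closer match to 2a, which nests participants within centre. Under this SD, an observed difference between 0.056 and 0.157 m/s at 17 per arm would be statistically significant and still inside limits of ±0.157 m/s. The limits stay the same in every row.

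**5. Precision of the limits.** With 21 pairs and a difference SD of 0.08, the standard error of one limit is 0.08 × √(1/21 + 1.96²/(2 × 20)) = 0.0303. Multiplied by t(20) = 2.086, this gives a 95% CI of about ±0.063 m/s around each limit.

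**The case against.** The strongest reply is that section 6.iv states no decision rule. It calls the limits a basis for evaluation; it does not say that an effect inside them counts as noise. The limits enter no model, test or sample size. The treatment-by-time effect would be estimated and tested exactly as planned. This stands, and it confines the point to interpretation.

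A reader might infer that the trial's target effect is bound to be dismissed, because ±0.157 m/s is about twice 0.08. The documents do not support that. The figure needs a test-retest SD of 0.08, and section 6.i does not label its SD so. If that SD describes change with training, it includes true differences in response and is more like an upper bound for retest noise. At an SD of about 0.041 or below, the effect clears the limits. Nor can the result be extended to every outcome, since only gait speed has planning figures. Applying it to 3a is also an inference from labels that do not match.

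The authors can add that section 6.iv already tests for a systematic repeat-measurement effect and considers correcting for it, and that it openly calls the sample small for practical reasons. Both are true. Neither makes an individual limit suitable for judging a mean.

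**Conclusion.** The point holds as a flaw in the stated yardstick, not as a flaw in the efficacy test. Section 6.iv ties the evaluation of randomised group effects to a quantity that describes single patients, does not fall with sample size and is not a meaningful change. A real benefit could therefore be read as within measurement noise.

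For gait speed, that possibility arises whenever the test-retest difference SD exceeds about 0.041 m/s. The protocol gives no value, so whether it would arise in this trial is unknown. The comparison with the standard errors assumes an SD of 0.08 and simple two-group formulas.

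This is not a detail left for the statistical analysis plan: the protocol fixes the yardstick, and a plan that follows it would inherit the problem. It should be fixed before results are seen, but it does not threaten the validity of the primary test.

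**What to change.** Replace the last sentence of the analysis technique in section 6.iv with, for example:

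> Between-arm effects are interpreted by the mixed-model estimate and its 95% CI, against zero and, where one is pre-stated with its justification, a group-level important difference. Limits of agreement are used only to interpret change in individual patients (section 6.x). The mean T-1 to T0 change with its 95% CI is used to interpret pooled pre-post change.

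The 0.08 m/s of section 6.i may be shown alongside as the expected effect. It should not be labelled a minimal important difference, because section 6.i presents it as an expectation drawn from literature reporting gains up to that size.

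The last sentence of the replacement largely builds on the paired comparison already planned. The cost is a small amount of wording and no new data. If the limits are also used to classify individuals as improved or not, section 6.x gains one minor step, since it compares those groups now without giving a threshold.

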## **v. Case-control study (1b)**

### **Population:**

21 (min. 17 for analysis) PD patients (To) randomly selected from total sample

21 (min. 17 for analysis) healthy controls age- and sex-matched to PD group

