## vii. Pre-Training (To)

Prior to the *training phase*, participants in all groups across all centers will undergo a standardized *functional assessment*, including measurement of clinical outcomes and a gait analysis during which EEG, EMG and kinematics data will be collected. A video of the participants head will be taken to determine the electrode position. In particular, a computer vision algorithms will detect the position of each electrode in 3D in relation to anatomical landmarks. This will allow a standardized 2D cartesian projection that could be shared across centers for statistical analysis. Please note that no video files will be shared, only 2D coordinates will be, which do not contain any personalized information.

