### **Analysis technique:**

Initially, independent t-tests and for EEG data cluster-based permutation tests time locked to the gait cycle will be used to compare patients to controls. The presence of and direction of differences between groups will facilitate interpretation for any effects found in analyses 2a - 2c. For this no corrections for multiple comparisons will be made. However, to present overall differences between groups we will reduce dimensionality of the set of primary and secondary clinical outcomes by means of PCA and use stepwise logistic regression on PC-scores to assess between group differences. For feedback control variables and neural correlates we will separately correct for multiple comparisons.

vi. SDTT vs. SDTT+ (2a)

Added value of additional component (SDTT+) to Speed Dependent Treadmill Training (SD Analysis technique.

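### Analysis 1b compares the healthy controls with a random 21 of the 126 planned PD patients although all are assessed at T0, a loss of precision for which the protocol gives no reason

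*Protocol*

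**What the plan says.** Protocol section 6.v (Population) defines the two groups of analysis 1b as "21 (min. 17 for analysis) PD patients (To) randomly selected from total sample" and "21 (min. 17 for analysis) healthy controls age- and sex-matched to PD group". Under Analysis technique the contrasts are unpaired: "independent t-tests and for EEG data cluster-based permutation tests time locked to the gait cycle will be used to compare patients to controls". A second step applies principal components and stepwise logistic regression to summarise the overall group difference.

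Section 5.vii (Pre-Training) states that "participants in all groups across all centers will undergo a standardized" functional assessment at T0, covering clinical outcomes, kinematics, EEG and EMG. Section 6.i plans the total: "Overall, 126 patients at all clinical sites will in enrolled over a period of 24 months".

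Section 6.viii (analysis 3b) takes 126 PD patients as its population. It uses changes from T0 in the same families of variables as 1b: gait speed and stride parameters, foot-placement feedback variables, beta power and EEG-EMG coherence.

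Section 6.ii explains that 1b is there to help interpret effects in the PD group, given that there is no placebo arm. The Trial Summary says the healthy controls are recruited at Amsterdam. Section 5.ii says that only Bologna, Kiel, Sydney and Tel Aviv actively recruit and train.

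**The concern.** The T0 variables that 1b needs will exist for the whole PD sample, because 3b cannot be run without them. Drawing 21 patients at random leaves 126 − 21 = 105 assessed patients out of this comparison (109 if only 17 are analysed), and no reason is stated. The pragmatic argument for a small sample in section 6.iv concerns the additional baseline measurement in 1a. It does not carry over to 1b, which needs no new measurement in patients. The figures 17 and 21 are those of the randomised sample-size calculation in section 6.i; 1b has no calculation of its own.

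At stake is the precision of the PD-versus-control contrasts. The protocol intends to use both the presence and the direction of group differences when reading analyses 2a to 2c, so a real deficit that goes undetected makes 1b less useful for that purpose.

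**Working it through.** **Where 17 and 21 come from.** Section 6.i assumes a difference of 0.08 m/s and an SD of 0.08 (d = 1.0), alpha 0.05 (taken as two-sided), power 0.80 and 1:1 allocation. The exact t calculation gives 17 per group (power 0.807; 0.781 at 16). Then 17 × 1.2 = 20.4, rounded up to 21. The figures reproduce, but they belong to the randomised comparison.

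**Standard error with a common SD.** SE = SD × √(1/n_PD + 1/n_HC).

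| PD v controls | SE (in SD) | Detectable d, 80% power, two-sided 0.05 |
|---|---|---|
| 21 v 21 (planned) | √(1/21 + 1/21) = 0.309 | 0.89 |
| 126 v 21 | √(1/126 + 1/21) = 0.236 | 0.66 |
| 17 v 17 (stated minimum) | 0.343 | 0.99 |
| 101 v 17 (20% loss from both groups) | 0.262 | 0.74 |

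The ratio is 0.3086/0.2357 = 1.309, so the planned SE is about 31% larger. The ratio at the minimum numbers is 1.308. Power at d = 0.7 is 60% with 21 v 21 and 84% with 126 v 21; at d = 0.8 it is 72% and 92%.

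**Unequal SDs.** The documents give no SDs by group. With r = SD_PD/SD_HC, the ratio is √(r²/21 + 1/21) / √(r²/126 + 1/21).

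| r | Inflation of planned SE |
|---|---|
| 0.5 | 10% |
| 0.75 | 20% |
| 1.0 | 31% |
| 1.5 | 54% |
| 2.0 | 73% |

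**Site effects.** The documents give no intraclass correlation (ICC), so a range is assumed. Site shares follow Table 2 (42, 42, 21 and 21 of 126), and the sum of squared shares is 2 × (1/3)² + 2 × (1/6)² = 0.278. The control site carries its own site effect. The variance of the contrast is then ICC × 0.278 + (1 − ICC)/n_PD + ICC + (1 − ICC)/21.

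| Assumed ICC | SE, 21 v 21 | SE, 126 v 21 | Inflation |
|---|---|---|---|
| 0.02 | 0.345 | 0.283 | 22% |
| 0.05 | 0.393 | 0.342 | 15% |
| 0.10 | 0.462 | 0.422 | 10% |

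**Does matching make up the loss?** Not as planned, because the tests are unpaired. A paired test on 21 pairs has SE = √(2(1 − ρ)/21). It would need a within-pair correlation ρ of about 0.42 to equal 126 v 21.

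**Does the pooled t-test survive 126 v 21?** Simulated type I error at nominal 5% (40,000 normal data sets per cell):

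| r | Pooled, 126 v 21 | Welch, 126 v 21 | Pooled, 21 v 21 |
|---|---|---|---|
| 0.5 | 21.6% | 5.1% | 5.2% |
| 0.75 | 11.0% | 5.0% | 5.0% |
| 1.5 | 1.0% | 5.1% | 5.0% |
| 2.0 | 0.2% | 5.0% | 5.3% |

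Using all patients therefore requires unequal-variance standard errors.

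**The case against.** A balanced, age- and sex-matched comparison is a conventional design. It gives a valid contrast, and nothing in section 6.v contradicts itself. Equal group sizes also protect the ordinary t-test against unequal variances, which 126 v 21 with a pooled variance does not. Group is fully confounded with site, and more PD patients cannot reduce an effect of the control site. All of this stands. It limits the size of the gain and determines the form of the fix, but it gives no reason to leave out patients already assessed.

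Four stronger readings are tempting, and the documents do not support them.

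- A reader might infer that every 1b contrast loses exactly 31%. That figure applies to the t-test contrasts with equal SDs and no site effect. The EEG permutation tests and the principal-component step also lose information, but not by that figure.
- A reader might infer that the other patients' data are thrown away. They go unused only in 1b; the longitudinal models and analyses 3b and 3c use them.
- A reader might count dependence on which 21 are drawn as a further fault. It is ordinary sampling variation, already within the standard error.
- A reader might infer that a missed deficit would lead to a training effect being judged as restoring nothing. No section gives 1b that role. Section 6.iv makes the limits of agreement from 1a the basis for judging effect sizes.

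**Conclusion.** The point holds as a matter of efficiency. Section 6.v fixes a PD group one sixth the size of the one that will be available, without stating a reason. The 31% is a reference value; the realistic loss depends on the SD ratio and site correlation, and across the ranges shown (each varied alone) it is never below about 10%. The calculations also assume independent observations within site and T0 data from all 126 planned patients. Section 5.vii expects about 5% not to attain the fixed treadmill speed, which barely changes the ratio.

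The planned comparison is not biased by the random draw, and the randomised comparisons of SDTT+ with SDTT are untouched. The change is worth making because it needs no further patients, visits or measurements.

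**What to change.** In section 6.v, define the 1b PD group as all PD participants with T0 data. Compare it with the healthy controls in a model adjusted for age and sex, with Welch-type or heteroscedasticity-robust standard errors, and use a studentised statistic in the EEG cluster-permutation tests. Keep the matched random-21 comparison as a sensitivity analysis. State that group is confounded with site because the controls come only from Amsterdam, and that a larger PD group does not remove this.

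Control recruitment can keep its present matching target; covariate adjustment covers the remaining imbalance. The cost is a change of wording and slightly more analysis work. The downside is reliance on the adjustment model wherever the controls do not match the age and sex distribution of the whole PD sample, which is why the matched comparison should be retained.
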